### 4.2. Non-Inclusion Criteria for Study Participants

Age < 18 years.Known result of a specific diagnostic examination for PE (D-dimer test, thoracic CT angiography, pulmonary scintigraphy, or venous ultrasound of the lower limbs).Hemodynamic instability (systolic blood pressure < 90 mmHg or more than 40 mmHg lower than usual for more than 15 min).Curative dose of anticoagulant in place for more than two days prior to inclusion.3-month follow-up not possible.Pregnant or parturient patient.Patient in detention by judicial or administrative decision.Patient undergoing compulsory psychiatric treatment.Patient placed under a legal protection measure.Patient incapable of giving free and informed consent.

## 5. Experimental Plan and Randomization

SPEED&PEPS will be an open-labelled cluster-randomized study, with 10 centers being allocated to the control group and 10 centers to the interventional group. Before randomization, participating centers will perform a preliminary assessment of the number of patients being investigated for suspected PE per month and of the rate of imaging test performed in patients suspected of PE in order to have an accurate idea of their baseline status [20]. These two criteria will be applied as stratification criteria during randomization to assure comparability between groups. 

SPEED&PEPS will be a pragmatic trial as confirmed by the PRECIS-2 rating of 42 out of 45 on the scale, with 0 corresponding to a fully explanatory study and 45 to a fully pragmatic study (cf. supplemental material) [24]. 

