## 9. Statistical Analysis

### 9.1. General Considerations 

Population characteristics will be described using their mean/standard deviation, median/interquartile range, or percent/95% confidence interval, as appropriate. Univariate comparisons will be made using Student’s, Mann–Whitney, or Fisher’s exact tests, as appropriate. The alpha risk will be set at 5%. All tests will be one-sided. Given that some proportions are expected to be small, confidence intervals will be calculated using the Clopper and Pearson exact method. 

The analysis will be performed using R software (R Foundation for Statistical Computing; 2008. http://www.R-project.org (accessed on 1 November 2022)) and its PropCIs and MASS add-ons (http://CRAN.R-project.org/package=PropCIs (accessed on 1 November 2022)). All objectives will be analyzed on the overall included population (intention-to-treat). A complementary per-protocol analysis will be performed, especially for the 4PEPS strategy in the interventional group. 

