### 9.2. Primary Statistical Analysis

The two main endpoints will be analyzed in a hierarchical manner. Firstly, non-inferiority will be analyzed on the safety endpoint with a non-inferiority limit set at 1.5%. If and only if confirmed, superiority analysis on the efficacy endpoint will be performed. Analyses will be performed using a mixed-effects logistic regression in line with recommendations for this type of study [26]. Missing data will be analyzed in order to determine whether they are informative and whether they are likely to cause a potential screening or information bias. 

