### 10.2. Efficacy Endpoint 

Considering the participation of 20 centers, an alpha risk of 5%, a power of 80%, an intra-center correlation coefficient of 0.05, and a usage rate of thoracic imaging of 45% in the control group, it will be necessary to include 2128 patients to demonstrate a relative decrease (1-sided analysis) greater than or equal to 20% (an absolute decrease of 9%) between the control and interventional groups in the usage rate of thoracic imaging. 

The intra-center correlation coefficient will be set at 0.05, given that the use of imaging is strongly linked to professional practices, which themselves vary significantly between centers. We estimate that it will be 45% in the control group and 36% in the interventional group on the basis of a previous retrospective assessment [15].

This means the figures previously calculated (2560 patients) will be sufficient for the hierarchical analysis of this endpoint. Nevertheless, an analysis of the usage rate of thoracic imaging in the control group will be performed after the inclusion of 1500 patients, i.e., 750 patients in the control group. If this rate is lower than expected (<45%), a reassessment of the sample size will be performed in order to assure a power of 80% to demonstrate a relative decrease of at least 20% between the control and the interventional groups on the usage rate of thoracic imaging.

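### The imaging analysis should state that it adjusts for the centre baseline imaging rate and volume used to stratify randomisation; on the plan's inputs, between-centre variance holds efficacy power to about 53% without adjustment

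*Protocol article*

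**What the plan says.** Section 5 of the protocol article sets out a pre-randomisation step: "participating centers will perform a preliminary assessment of the number of patients being investigated for suspected PE per month and of the rate of imaging" tests. It then says: "These two criteria will be applied as stratification criteria during randomization to assure comparability between groups". Allocation is by centre, "with 10 centers being allocated to the control group and 10 centers to the interventional group".

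Section 9.2 describes the analysis of both primary endpoints in one sentence: "Analyses will be performed using a mixed-effects logistic regression in line with recommendations for this type of study". It names no fixed effects, so the stratification criteria are neither included nor ruled out.

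Section 10.2 sizes the imaging endpoint on 45% versus 36% with "an alpha risk of 5%, a power of 80%, an intra-center correlation coefficient of 0.05". It explains the ICC by saying that "the use of imaging is strongly linked to professional practices, which themselves vary significantly between centers". Section 9.1 adds: "All tests will be one-sided". The stated requirement is 2128 patients, and section 10.2 treats the planned 2560 as enough. Neither figure is said to rest on baseline adjustment.

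**The concern.** The baseline imaging rate is a direct pre-trial measure of the centre habit that section 10.2 gives as the reason for the ICC of 0.05. It is collected before allocation and thought important enough to stratify on. Yet the stated analysis does not say that it is used again.

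This matters more here than in most trials. With 20 centres and an ICC of 0.05, differences between centres, not patient numbers, set the precision of the imaging comparison. More patients in the same centres gain almost nothing, so the reassessment planned after 1500 patients cannot secure 80% power by extending recruitment alone. Either more centres are needed, or some of the between-centre variance has to be explained. Only the second uses data the trial already plans to hold.

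**Working it through.** **Inputs.** From section 10.2: 45% versus 36%, alpha 5% one-sided, ICC 0.05, 20 centres. From sections 5 and 10.1: 10 centres and 1280 patients per arm, so 128 per centre on average. *Assumed, not in the article:* the correlation r between a centre's baseline imaging rate and its trial-period rate, shown from 0.5 to 0.8. Volume is assumed to explain nothing further.

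**1. The plan's own figure.** Without clustering, 367 patients per arm are needed (pooled null variance; 365 unpooled). At 2128/20 = 106.4 patients per centre the design effect is 1 + 105.4 × 0.05 = 6.27. The total is then 2 × 367 × 6.27 ≈ 4602, so 2128 does not reproduce. It would correspond to a design effect of 2128/734 = 2.90, that is, an ICC of 1.90/105.4 ≈ 0.018.

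**2. Power without adjustment.** The design effect at 128 per centre is 1 + 127 × 0.05 = 7.35, so the effective n per arm is 1280/7.35 = 174. The standard error is √[(0.45 × 0.55 + 0.36 × 0.64)/174] = √(0.4779/174) = 0.0524. Power = Φ(0.09/0.0524 − 1.645) ≈ 53%. With a noncentral t on 18 df it is 50%.

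**3. Ceiling.** With unlimited patients the effective n per arm tends to 10/0.05 = 200, well below 365. Power there is at most 58% (t: 55%).

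**4. Power with adjustment.** Residual ICC = 0.05 × (1 − r²); design effect = 1 + 127 × residual ICC; power as in step 2. The t figures use 16 df once two centre-level covariates are fitted.

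| r | Variance explained (r²) | Residual ICC | Design effect | Effective n per arm | Power, normal | Power, t |
|---|---|---|---|---|---|---|
| none | 0 | 0.050 | 7.35 | 174 | 53% | 50% (18 df) |
| 0.5 | 0.25 | 0.0375 | 5.76 | 222 | 62% | 58% |
| 0.6 | 0.36 | 0.032 | 5.06 | 253 | 66% | 63% |
| 0.7 | 0.49 | 0.0255 | 4.24 | 302 | 73% | 70% |
| 0.8 | 0.64 | 0.018 | 3.29 | 390 | 82% | 79% |

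Using the pooled null variance changes these by less than one point (61% instead of 62% at r = 0.5).

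**5. What 80% requires.** An effective n of 367 needs a design effect of 1280/367 = 3.49, hence a residual ICC of 2.49/127 = 0.0196 and a share explained of 1 − 0.0196/0.05 ≈ 0.61. The t reference with 16 df raises this to about 0.65. As correlations these are √0.61 ≈ 0.78 and √0.65 ≈ 0.81.

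**6. Price of the adjustment.** If the covariates explained nothing, moving from 18 to 16 df at the same noncentrality (0.09/0.0524 ≈ 1.72) would lower t power from 50.3% to 50.0%.

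These are risk-difference approximations with equal centre sizes, not a simulation of the logistic mixed model. They show the order of the gain.

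**The case against.** The strongest objection is that this is a condensed article. Section 9.2 names a class of model and follows a cited recommendation. It lists no terms at all, not even treatment arm. A covariate list commonly sits in the full protocol or SAP, which are not shown. A reader might infer that the trial has decided to leave out the baseline data, or that it will not analyse as randomised. The article supports neither reading: stratifying centres and fitting a mixed model are compatible, and nothing is excluded. Leaving stratification factors out would also usually cost efficiency, not validity. All of this stands, and it is why the point is a recommendation to state the terms, not a charge of error.

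The size of the gain is also open. Several design features could lower r. Intervention centres are asked to change practice. Control centres receive guideline reminders and the decision-support software. The baseline assessment is of unstated length and covers patients under investigation, whereas trial patients must be eligible and consent. At r = 0.5 to 0.7 the trial stays short of 80% even after adjustment. Nothing in the article links volume to imaging use, so the case for including volume is only that it is a randomisation criterion.

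Finally, the 53% follows from the sample-size calculation, not from how the covariates are described. That shortfall is a separate matter and should not be counted twice. It is used here only to show why the choice of covariates matters in this trial.

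**Conclusion.** The point holds as a concrete, nearly free improvement, with moderate confidence. The article collects and stratifies on two centre measures, does not state that they enter the primary model, and sizes the trial on the full ICC of 0.05. Under its own inputs, unadjusted efficacy power at 2560 patients is about 53% (t: 50%). Adjustment for the baseline imaging rate would bring it to about 62–82% (t: 58–79%) for an assumed r of 0.5 to 0.8. It reaches 80% only if about 61–65% of the between-centre variance is explained, so it helps materially but cannot be relied on to rescue the power claim.

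Two wider readings are not supported. Because an ICC of about 0.018 would yield 2128, a reader might infer that the plan has already allowed for adjustment at r = 0.8; section 10.2 states 0.05 and mentions no such allowance. A reader might also expect a similar gain for the safety endpoint. With an ICC of 0.002 and an event rate of about 1.5% (section 10.1), there is little between-centre variance to remove.

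**What to change.** State in section 9.2 that the imaging model has fixed effects for arm, the centre's baseline imaging rate (entered as a continuous covariate) and baseline monthly volume, with a random centre intercept. If the full protocol or SAP already says so, no change is needed beyond confirming it.

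The cost is a sentence and about two of the 18 centre-level degrees of freedom. No new data are required. The statement should not be presented as making 2560 patients sufficient: any power credited to adjustment needs a stated baseline-to-trial correlation and its basis.

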## 6. Description of Study Intervention

### 6.1. Comparison Strategy: Control Group

The investigating physicians of the participating centers in the control group will be free to provide care as they see fit. However, a reminder of national and European guidelines for PE management will be given to them and they will have the recommendation to apply a validated strategy [3,4,5]. To make it easier, the different scores will be included in the clinical help–decision support software called SPEED [23]. Investigators will be asked to enter data about the included patients directly into SPEED, which will act as the study’s electronic case report form (eCRF). A paper version of the CRF will also be available. 

### 6.2. Strategy under Study: Interventional Group

Physicians of the participating centers in the intervention group will have the recommendation to apply the 4PEPS strategy. To make it easier to apply, the 4PEPS score will be included in SPEED [23]. Investigators will be asked to enter the information relating to patients included in the study directly into SPEED before performing any testing. Entering these data will enable the 4PEPS score to be calculated automatically and specific recommendations to be provided. A paper version of the CRF will also be available.

### 6.3. Associated Care and Treatment 

For the duration of the study, physicians will be free to treat and refer patients with a diagnosis of PE. However, they will be reminded of practice guidelines on VTE treatment [3,4,5]. These recommendations will also be accessible via the SPEED clinical decision support tool.

## 7. Study Participant Follow-Up 

Data relating to care at the emergency department and the eventual subsequent hospitalization (characteristics, comorbidities, clinical and paraclinical data, confirmed diagnosis or diagnoses, possible adverse events, and treatment) will be compiled and entered into the eCRF. At discharge from the hospital, patients will be instructed to return to the ED or to contact their family physician in the event of any symptoms that may suggest a possible thromboembolic event or bleeding.

Patients and/or their relatives and family physician(s) will be contacted by phone and/or post or email at the end of the 3-month follow-up period. Using a standardized questionnaire, they will be asked about whether a thromboembolic event or bleeding has occurred; what examinations, consultations, or hospitalizations have taken place; and whether anticoagulant treatment has been introduced. Examination results (biological tests including D-dimer, ultrasonography, thoracic imaging…), hospital discharge summaries, and circumstances and causes of death, if any, will be collected. For each possible event during the follow-up, an adjudication file will be constituted, including reports of all relevant exams. All possible events will be adjudicated by the independent committee, blinded of randomization arm (control or interventional group). 

## 8. Medico-Economic Analysis

The medico-economic analysis will be performed following the recommendations of the French National Authority for Health (HAS) (https://www.has-sante.fr/portail/jcms/r_1499251/fr (accessed on 1 November 2022)) and the CHEERS (Consolidated Health Economic Evaluation Reporting Standards) statement [25]. A cost–efficacy analysis will be performed, aimed at comparing the efficacy of applying the 4PEPS strategy against usual practices in terms of cost for each serious event avoided, from the perspective of health insurance. The timescale will be 90 days corresponding to the evaluation period of the efficacy endpoint.

The result will be shown as a differential cost–efficacy ratio and expressed as a cost per serious event avoided within 90 days (serious adverse event of PE testing, PE-related death, thromboembolic event, or major bleeding). This evaluation will be performed at D90 via a telephone call using a standardized questionnaire.

The evaluation of costs will concern the use of hospital and outpatient treatments and medical equipment (medications and medical devices). 

## 9. Statistical Analysis

### 9.1. General Considerations 

Population characteristics will be described using their mean/standard deviation, median/interquartile range, or percent/95% confidence interval, as appropriate. Univariate comparisons will be made using Student’s, Mann–Whitney, or Fisher’s exact tests, as appropriate. The alpha risk will be set at 5%. All tests will be one-sided. Given that some proportions are expected to be small, confidence intervals will be calculated using the Clopper and Pearson exact method. 

The analysis will be performed using R software (R Foundation for Statistical Computing; 2008. http://www.R-project.org (accessed on 1 November 2022)) and its PropCIs and MASS add-ons (http://CRAN.R-project.org/package=PropCIs (accessed on 1 November 2022)). All objectives will be analyzed on the overall included population (intention-to-treat). A complementary per-protocol analysis will be performed, especially for the 4PEPS strategy in the interventional group. 

### 9.2. Primary Statistical Analysis

The two main endpoints will be analyzed in a hierarchical manner. Firstly, non-inferiority will be analyzed on the safety endpoint with a non-inferiority limit set at 1.5%. If and only if confirmed, superiority analysis on the efficacy endpoint will be performed. Analyses will be performed using a mixed-effects logistic regression in line with recommendations for this type of study [26]. Missing data will be analyzed in order to determine whether they are informative and whether they are likely to cause a potential screening or information bias. 

### 9.3. Secondary Statistical Analysis

The confidence interval of the false-negative rate with the 4PEPS strategy will be calculated on an intention-to-treat basis and then on a per-protocol basis, and its upper limit will be compared with the limit considered acceptable by the ISTH recommendations based on the prevalence in the study: 1.82 + 0.00528* prevalence, i.e., for a prevalence of 14%, an upper limit ≤1.89% [16]. 

Hierarchical analysis of the other secondary outcomes will be conducted using a mixed effects logistic regression. If the primary safety endpoint and then the primary efficacy endpoint are confirmed, the false-negative rate with the 4PEPS strategy will be compared to that of the usual approaches in the control group using a mixed-effects logistic regression with a non-inferiority limit set at 1.35% [27]. If this endpoint is confirmed, then the two other secondary endpoints will be analyzed using the Holm procedure for multiple testing correction.

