### 3.2. Secondary Objective(s) and Endpoint(s)

The first secondary objective is to demonstrate that the risk of false-negative diagnosis with the 4PEPS strategy is very low in accordance with the ISTH criteria for validation of rule-out PE diagnostic strategies. The endpoint will be the false-negative rate defined as the rate of thromboembolic events occurring in the 90 days following inclusion in patients for whom PE was ruled out according to the 4PEPS strategy and who were not treated with anticoagulants. ISTH recommendations state the upper limit of the 95% confidence interval (95%CI) of this 90-day thromboembolic event rate should be less than 1.82 + 0.00528* prevalence, i.e., a rate ≤1.89% for a prevalence of 14% [16].

The second secondary objective is to demonstrate that the 4PEPS strategy (intervention group) is not inferior to current practices (control group) as regards the risk of false-negative diagnosis. The false-negative rate will be defined as the rate of thromboembolic events occurring in the 90 days following inclusion in patients for whom PE was ruled out and who were not treated with anticoagulants. 

The other secondary objectives are to evaluate and compare to usual practice the impact of the 4PEPS strategy as regards the rate of D-dimer measurement and the length of time spent in the emergency department by patients with suspected PE.

The ancillary objectives are to assess the rate of incidental findings on CTPA, the acceptance by physicians and their use in everyday practice of the clinical decision support tool SPEED [23], as regards the rate of patients for whom the SPEED application is used in real time (i.e., when the data that enable the automatic calculation of the clinical probability and the reminder of the appropriate diagnostic strategy have been entered before any additional examinations are performed, in particular, the D-dimer test); and to evaluate the appropriateness of diagnostic management according to international guidelines and if it differs when the SPEED application is used in real time or not. 

We will also evaluate and compare to usual practice the medico-economic impact of the 4PEPS strategy in terms of cost per serious clinical event related to the diagnostic procedure avoided in the 90 days following inclusion (cost–efficacy analysis). The endpoint will be the differential cost–efficacy ratio at 90 days.

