The hierarchical analysis applied in SPEED&PEPS will allow us to address the questions of efficacy and safety without increasing the alpha risk through multiple tests. If our research hypothesis is confirmed, this will have a major impact for patients and for public health. For patients, the reduction in the use of imaging tests will make it possible to limit the cumulative radiation exposure, the impact of which is now known in terms of the risk of radiation-induced cancer, in particular breast cancer, for women. It will reduce the time it takes to manage patients with suspected PE in the emergency department, as patients that undergo thoracic imaging take an average of 4 h longer to treat than those who do not require it. Our study will thus have an indirect impact on other patients by limiting the overcrowding of emergency departments. Lastly, given the frequency of suspected pulmonary embolism in emergency departments and the very high usage rate of CT angiographies (80% in a recent observational study [10]), the SPEED&PEPS study should result in substantial savings in terms of the direct cost of diagnostic investigations and the indirect cost of hospitalizations due to waiting times or delayed harmful effects. We expect the cost per serious clinical event avoided in relation to the diagnostic approach to be very favorable compared to current practices.

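### Section 9.3 names a mixed-effects logistic model for all the other secondary outcomes, but emergency department (ED) length of stay is a duration with no cut-off; the model for it, and the tested direction of both Holm endpoints, need stating

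*Protocol article*

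**What the plan says.** Section 3.2 of the protocol article lists two false-negative objectives first. It then continues: "The other secondary objectives are to evaluate and compare to usual practice the impact of the 4PEPS strategy", the endpoints being "the rate of D-dimer measurement and the length of time spent in the emergency department by patients with suspected PE". ED time is not defined there, or elsewhere, as exceeding a threshold.

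Section 9.3 treats the two false-negative analyses individually. For the remainder it says "Hierarchical analysis of the other secondary outcomes will be conducted using a mixed effects logistic regression". If the false-negative non-inferiority comparison succeeds, "then the two other secondary endpoints will be analyzed using the Holm procedure for multiple testing correction".

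Section 9.1 sets alpha at 5% and adds "All tests will be one-sided". It also lists Student, Mann–Whitney and Fisher tests for univariate comparisons, straight after describing how population characteristics will be summarised.

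The Discussion (section 12) says of reduced imaging that "It will reduce the time it takes to manage patients with suspected PE in the emergency department", because "patients that undergo thoracic imaging take an average of 4 h longer to treat than those who do not require it".

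**The concern.** A logistic model is a model for a binary outcome (or, in its ordinal form, an ordered one). Time in the ED is neither as defined, so the analysis named for a multiplicity-controlled endpoint does not match it. This is a mismatch in stated text, not detail left to an analysis plan: the article names a model, and the model does not suit one of the two endpoints it has to cover.

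At stake is how far a claim of shorter ED stay was fixed in advance. As the text stands, the analyst must depart from the named model or create a binary version of the endpoint, and either choice could be made after the data are seen. The Holm step ties the two endpoints together: with two tests at a total one-sided 5%, the smaller p-value is compared with 5%/2 = 2.5%, and the larger with 5% only if the first succeeds. An undefined p-value for ED time therefore also leaves open which threshold applies to the D-dimer rate. A one-sided test further needs its direction written down before analysis.

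**Working it through.** The article gives no standard deviation, effect size, power or intra-centre correlation for ED time, so there is no planned figure to reproduce. The check is a comparison of passages.

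**1. Which endpoints are in the Holm step?** Section 3.2 has four secondary endpoints:
- the false-negative rate under 4PEPS against the ISTH limit;
- the false-negative rate compared between arms;
- the D-dimer measurement rate;
- ED length of stay.

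Section 9.3 deals with the first by a confidence interval and the second by a non-inferiority comparison with a 1.35% limit. 4 − 2 = 2 remain, matching its reference to two other endpoints. Ancillary and medico-economic objectives are described separately. The Holm pair can only be the D-dimer rate and ED time.

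**2. Does the named model fit each?**

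| Endpoint | Type | Mixed-effects logistic model |
|---|---|---|
| D-dimer measurement rate | binary per patient | fits |
| ED length of stay | duration, no cut-off | does not fit |

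As a plain confirmation, a standard logistic fit to simulated durations in minutes (log-normal values assumed for illustration) was refused by the software, because the outcome must lie between 0 and 1.

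**3. Does another passage supply the method?** The only tests for continuous data are Student and Mann–Whitney in section 9.1. Section 5 randomises centres, 10 per arm. Both tests treat patients as independent, so neither respects the design. Section 12 itself says that cluster-randomised studies need particular analysis. These tests are therefore not a suitable fallback, and section 9.3 does not assign them.

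**4. Is the one-sided direction fixed?**

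| Place | ED time | D-dimer rate |
|---|---|---|
| Section 3.2 (objective) | evaluate and compare, no direction | evaluate and compare, no direction |
| Sections 9.1 and 9.3 (analysis) | one-sided, direction not given | one-sided, direction not given |
| Section 12 (Discussion) | reduction expected | not mentioned |

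For ED time the direction can be inferred from the Discussion. For the D-dimer rate no direction is stated anywhere.

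**The case against.** The strongest defence is that this is loose wording. Section 9.3 calls for a mixed-effects model, which shows that clustering is meant to be handled. A continuous-outcome mixed model could be specified in an analysis plan that is not shown. An ordinal (proportional-odds) mixed logistic model would even avoid a single cut-point. The endpoint is also tested only after primary safety, primary efficacy and false-negative non-inferiority have all succeeded. Most of this stands and limits the weight of the point. It does not remove it: the article names one model for both endpoints, does not say that an ordinal version is meant, and leaves no method in the text that suits ED time.

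A reader might infer more, and the documents do not support it:

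- **That ED time has no direction at all.** The Discussion expects a reduction and gives the reason.
- **That the type I error will be badly inflated.** With 2560/20 = 128 patients per centre and the imaging correlation of 0.05 from section 10.2 borrowed for ED time, the design effect is 1 + 127 × 0.05 = 7.35. An unclustered test at nominal one-sided 5% would then have a true error of 1 − Φ(1.645/√7.35) ≈ 27%. At an assumed correlation of 0.01 the design effect is 2.27 and the error about 14%. The arithmetic is right, but it describes a test that section 9.3 does not assign, and neither correlation is given for ED time.
- **That a median split would keep only 2/π ≈ 64% of the information.** That holds for independent normal data. Under a latent-normal model the correlation of the split variable is (2/π)·arcsin(ρ). For ρ = 0.05 this is 0.032, the design effect is 5.04, and the retained information is 7.35/(5.04 × π/2) ≈ 93%. For ρ = 0.01 it is 2.27/(1.81 × π/2) ≈ 80%.
- **That the only choices are a data-driven cut-point or a test that ignores clustering.** A mixed model for a continuous time is an obvious third route.
- **That these two tests must become two-sided.** One-sided testing at 5% is the declared convention of the whole trial. That such a test cannot formally declare an increase is a property of every one-sided test; estimates would still show one.

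**Conclusion.** The point holds and is minor. The model named in section 9.3 does not fit ED length of stay, which is one of the two endpoints in the final confirmatory step, and section 9.1 offers no suitable substitute. The one-sided direction should be written down for both endpoints: for ED time it can be inferred from the Discussion, and for the D-dimer rate it is stated nowhere.

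The conclusion rests on reading the Holm pair as the D-dimer rate and ED time, which is the only reading that sections 3.2 and 9.3 allow together. No numerical size can be given, because the article contains no variance, correlation or target effect for ED time. Neither primary analysis nor the sample size of 2560 depends on it.

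**What to change.** In section 9.3:

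- Keep the mixed-effects logistic regression for the D-dimer measurement rate.
- For ED length of stay, name a mixed model suited to a skewed continuous outcome. One option is a linear mixed model on log time with a random centre intercept and a small-cluster degrees-of-freedom correction (20 centres − 2 arms = 18, or Kenward–Roger), reported as a ratio of geometric means with its confidence interval. A gamma mixed model would also serve; what matters is that one is fixed in advance.
- State the tested direction for both endpoints: a reduction for ED time, in line with the Discussion, and whichever direction the sponsor intends for the D-dimer rate.

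The cost is about two sentences. The article gives the trial status as not started, so the change can be made before any data exist. The hierarchy, the Holm step, the one-sided convention and the sample size stay as they are.
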